## Abstract

**Background:**

Treatment standard for patients with primary glioblastoma (GBM) is combined radiochemotherapy with temozolomide (TMZ). Radiation is delivered up to a total dose of 60 Gy using photons. Using this treatment regimen, overall survival could be extended significantly however, median overall survival is still only about 15 months.

Carbon ions offer physical and biological advantages. Due to their inverted dose profile and the high local dose deposition within the Bragg peak precise dose application and sparing of normal tissue is possible. Moreover, in comparison to photons, carbon ions offer an increase relative biological effectiveness (RBE), which can be calculated between 2 and 5 depending on the GBM cell line as well as the endpoint analyzed. Protons, however, offer an RBE which is comparable to photons.

First Japanese Data on the evaluation of carbon ion radiation therapy showed promising results in a small and heterogeneous patient collective.

**Methods/Design:**

In the current Phase II-CLEOPATRA-Study a carbon ion boost will be compared to a proton boost applied to the macroscopic tumor after surgery at primary diagnosis in patients with GBM applied after standard radiochemotherapy with TMZ up to 50 Gy. In the experimental arm, a carbon ion boost will be applied to the macroscopic tumor up to a total dose of 18 Gy E in 6 fractions at a single dose of 3 Gy E. In the standard arm, a proton boost will be applied up to a total dose 10 Gy E in 5 single fractions of 2 Gy E.

Primary endpoint is overall survival, secondary objectives are progression-free survival, toxicity and safety.

**Discussion:**

The Cleopatra Trial is the first study to evaluate the effect of carbon ion radiotherapy within multimodality treatment of primary glioblastoma in a randomized trial comparing this innovative treatment of the treatment standard, consisitng of photon radiotherapy in combination with temozolomide.

**Trial Registration:**

ISRCTN37428883 and NCT01165671

## Background

Glioblastomas (GBM) are the most common primary brain tumors in adults; they are characterized by a rapid and infiltrative growth pattern. In spite of extensive research over the past years, outcome of patients with GBM still remains unsatisfactory.

With surgery and supportive care alone, overall survival is about 3-5 months. Postoperative radiotherapy (RT) can increase overall survival to 9-12 months [1]. A number of studies have shown that an additional treatment with chemotherapy can increase overall survival. This benefit, however, is commonly associated with a high risk of treatment-related side effects, especially with combination treatments, such as PCV, and with carmustine (BCNU). Only recently, significant increase in overall survival could be achieved by adding temozolomide (TMZ), an orally applicable alkylating substance, to postoperative radiotherapy. In a prospective randomized Phase III study performed by the EORTC radiochemotherapy with TMZ was compared to postoperative radiation alone. Overall survival could be increased from 12.1 months to 14.6 months, with acceptable toxicity. TMZ was applied in a dose of 75mg/m^2^/die during radiotherapy, followed by 6 cycles of adjuvant TMZ [2]. Therefore, standard treatment of patients with GBM is currently considered to be postoperative radiochemotherapy with TMZ, followed by 6 cycles of adjuvant TMZ.

However, with an overall survival of about 15 months, treatment outcome still remains unsatisfactory. Therefore, a number of treatment concepts are currently under investigation.

Novel radiotherapeutic modalities such as carbon ion radiotherapy offer a promising treatment alternative. Radiation therapy using charged particles is characterized by distinct physical and biological characteristics. Charged particles provide the physical advantage of an inverted dose profile which enables steep dose gradients. Neighbouring organs at risk can be spared much better. Heavy charged particles, such as carbon ions, additionally offer an increased relative biological effectiveness (RBE).

Carbon ion radiotherapy was available by the Department of Radiation Oncology at the Gesellschaft für Schwerionenforschung (GSI) in Darmstadt since 1997. Superior treatment results for a number of tumor entities, such as chordomas and chondrosarcomas of the skull base, as well as adenoid cystic carcinomas (ACC) have been shown, and carbon ion radiotherapy is currently performed in the clinical routine for these patients [3-6]. Safety of carbon ion radiotherapy with respect to critical organs at risk, such as the brain, brainstem or spinal chord, have been shown in these studies. At the Heidelberg Ion Therapy Center (HIT), treatment of over 1300 patients per year with Proton and Carbon ion RT is possible.

In general, GBM are treatment-resistant tumors. Early studies using a high-dose proton boost could show that total doses up to 90 Gy E were effective in preventing local tumor recurrences, however, such high doses were associated with high rates of side effects [7].

In vitro data for the treatment of GBM with carbon ions have shown superior effectivity compared to photons [8]. Our own data have shown a high RBE for carbon ion RT for GBM; additionally combination of carbon ion radiotherapy and TMZ have been evaluated and show an additive effect in GBM-cell lines [9]. A first clinical study evaluating a carbon ion boost in patients with GBM was recently published by Mizoe et al. [10]. Median overall survival in patients with glioblastoma was 17 months; however, only small patient numbers were evaluated and standard chemotherapy with TMZ was not applied. In that study, the carbon ion boost was applied with stepwise increasing total doses up to 24.8 Gy E. While toxity was low even in the high dose arm, the data showed that patients seem to benefit from the high dosed carbon ion boost. Therefore, the concept of a carbon ion boost to patients with GBM with a macroscopic tumor lesion after neurosurgical resection is a promising treatment alternative and requires evaluation in a larger patient group with GBM. Additionally, the carbon ion boost should be evaluated in combination with standard radiochemotherapy with TMZ.

In the present CLEOPATRA trial, the impact of a carbon ion boost will be compared to a proton boost using intensity-modulated rasterscanning in patients with incompletely resected GBM in combination with standard radiochemotherapy with TMZ. TMZ will be continued during the standard and experimental arm as prescribed in standard photon radiochemotherapy.

Protons offer a comparable RBE to photons. A number of pre-clinical and clinical studies have shown that the effect of proton radiotherapy on normal tissue as well as on tumors is comparable to photon radiotherapy. The RBE values for clinical proton beams have been determined for a wide spectrum of *in vitro *as well as *in vivo *systems, as well as in clinical trials [11,12]. Therefore, it has been concluded that proton therapy can replace photon therapy without any further clinical trials when the same dose is applied [13]. In the current study, the proton dose applied is equivalent to the standard dose applied in conventional radiochemotherapy with photons. Moreover, protons and carbon ions are both characterized by the same physical characteristics, i.e. Bragg Peak with a high local dose deposition. This results in a reduction on dose to normal tissue in proton and carbon ion radiotherapy compared to conventional photon radiotherapy. These physical characteristics can be considered comparable for the proton and the carbon ion beam, and both are able to convey to improved dose distributions as compared to photons. Thus, reduction of side effects on normal tissue can be achieved by particle therapy (proton or carbon ion) compared to conventional photon radiotherapy. The aim of the present study however is not to evaluate the distinct physical characteristics, therefore it is essential that treatment techniques and physical characteristics are identical in both treatment arms. The aim of this study is solely to compare the effect of the increased RBE in the carbon ion arm on outcome. Therefore, the proton treatment arm is considered to be the standard treatment arm, and carbon ion radiotherapy is the experimental treatment arm.

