## Methods and Design

### Study design

The purpose of the trial is to compare a carbon ion boost to a proton boost delivered to the macroscopic tumor in combination with combined radiochemotherapy with TMZ in patients with primary GBM.

The aim of the study is to compare overall survival as a primary endpoint, and progression free survival, toxicity and safety as secondary endpoints.

Focus of the analysis is to evaluate the change in overall survival and local control by carbon ion radiotherapy. Therefore, the aim of the trial is to evaluate the improvement in outcome due to effect of the altered biology of carbon ions on GBM. Chemotherapy with TMZ is considered standard treatment and is administered continuously as it would be applied in standard patient care outside any trial.

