**Figure 1 F1:**
[figure not shown]
**Workflow diagram of the Cleopatra Study evaluation the role of carbon ion radiotherapy for the treatment of patients with primary glioblastoma**.

Patients fulfilling the inclusion criteria will be randomized into two arms:

Arm A - Experimental Arm

Carbon Ion Radiation Therapy as a Boost to the macroscopic tumor

Total Dose 18 Gy E, 6 fractions, 3 Gy E single dose

Arm B - Standard Arm

Proton Radiation Therapy as a Boost to the macroscopic tumor

Total Dose 10 Gy E, 5 fractions, 2 Gy E single dose

Standard chemotherapy with TMZ will be continued during the experimental and standard arm in conventional dosing of 75 mg/m^2 ^per day.

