### Dose Prescription Experimental (Carbon) Arm

The intensity-controlled rasterscan system will be used for beam application. Six fractions of a single dose of 3 Gy E up to a total dose of 18 Gy E will be prescribed to the maximum of the calculated dose distribution for the target volume (Boost). Treatment planning aims in the coverage of the target volume by the 90%-isodose line.

Dose specification is based on biologic equivalent dose because of the high relative biologic effectiveness (RBE) of carbon ions, which differs throughout the target volume due to its dependence on various factors. RBE will be calculated at each voxel throughout the target volumes and biological optimization will be performed. The dose prescription used is related to the isoeffective dose Gy E (Cobalt Gray equivalent) using daily fractions of 2 Gy and a weekly fractionation of 5 × 2 Gy.

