#### 3. Treatment effect size

The CLEOPATRA trial will be designed to detect an improvement of 20% (absolute) in survival rate after 12 months. The rationale behind this assumption is as follows: Carbon ion radiotherapy is characterized by a higher relative biological effectiveness (RBE) as compared to conventional photons or protons. Preclinical experiments on glioblastoma cell lines have shown that this RBE lies between 3 and 5, depending on the respective endpoint or cell line [9]. Therefore, the effect of carbon ion radiotherapy for the treatment of patients with primary glioblastoma is expected to be substantially higher than with conventional proton radiotherapy.

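### The stated aim is to isolate the effect of RBE, but the arms also differ in RBE-weighted dose, fraction size and fraction number, so a survival difference cannot be attributed to RBE alone

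*Protocol article*

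**What the plan says.** All references are to the protocol article.

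- **Aim.** Background: "The aim of this study is solely to compare the effect of the increased RBE in the carbon ion arm on outcome". The sentence before it explains that the distinct physical properties are not under study: "therefore it is essential that treatment techniques and physical characteristics are identical in both treatment arms". Study design, in Methods, restates the aim without the word *solely*: "the aim of the trial is to evaluate the improvement in outcome due to effect of the altered biology of carbon ions on GBM".
- **Arms.** Trial Design, below Figure 1, gives carbon as "Total Dose 18 Gy E, 6 fractions, 3 Gy E single dose" and protons as "Total Dose 10 Gy E, 5 fractions, 2 Gy E single dose".
- **Unit.** Dose Prescription Experimental (Carbon) Arm: "Dose specification is based on biologic equivalent dose because of the high relative biologic effectiveness (RBE) of carbon ions". RBE is calculated voxel by voxel, and Gy E is described as an isoeffective dose referred to 2 Gy daily fractions. Dose Prescription Standard (Proton) Arm uses an RBE of about 1.1 and notes that only this arm adds up to the conventional 60 Gy.
- **Effect-size rationale.** Item 3 of the sample size section supports the 20% absolute improvement with this statement: "Carbon ion radiotherapy is characterized by a higher relative biological effectiveness (RBE) as compared to conventional photons or protons". It cites a preclinical RBE of 3 to 5.

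**The concern.** Gy E already includes RBE, so equal Gy E in the two arms would be intended to be isoeffective. The arms are not equal in Gy E. Any survival benefit could come from a property of carbon that the weighting does not capture, from the extra effective dose, from the larger or more numerous fractions, or from a mixture of these.

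The article itself treats dose as a driver of outcome apart from particle type. The Background reports that high-dose proton boosts prevented local recurrence. It also says that patients in a Japanese carbon-ion study seemed to gain from the higher boost doses. And it accepts protons as a replacement for photons on condition that the dose is the same.

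What is at stake is the conclusion. A positive confirmatory test would invite a statement about RBE that the design cannot support. The problem is greatest for a positive result, because the additional dose is in the experimental arm.

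**Working it through.** **1. Reproduce the stated doses** (Trial Design and the two Dose Prescription sections; dose = fractions x dose per fraction).

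- Carbon: 6 x 3 = 18 Gy E, as stated.
- Proton: 5 x 2 = 10 Gy E, as stated.
- Standard-arm total: 50 + 10 = 60, as stated.

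**2. Contrast between the arms.**

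| | Carbon | Proton | Difference |
|---|---|---|---|
| Boost, Gy E | 18 | 10 | 8 (18/10 = 1.8) |
| Dose per fraction, Gy E | 3 | 2 | 1 (50% more) |
| Fractions | 6 | 5 | 1 |
| Total with 50 Gy photons | 68 | 60 | 8 (8/60, about 13%) |
| Total with 48 to 52 Gy photons | 66 to 70 | 58 to 62 | 8 for the same photon dose |

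The range of 48 to 52 Gy comes from the inclusion criteria. The 8 Gy E difference remains after RBE weighting in both arms.

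**3. Identifiability.** There is one randomised contrast and four features change with it: particle, total Gy E, fraction size and fraction number. They are fully aliased, so no model fitted to the two arms can separate them.

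**4. Fraction size (illustrative only).** Linear-quadratic conversion to 2 Gy fractions: EQD2 = n x d x (d + r) / (2 + r), where r is the alpha/beta ratio. The article gives no value, so r is assumed to lie between 10 and 2.

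- Carbon, r = 10: 18 x 13/12 = 19.5.
- Carbon, r = 2: 18 x 5/4 = 22.5.
- Proton, any r: 10.

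The difference would be 9.5 to 12.5. If Gy E is already isoeffective to 2 Gy fractions, as the carbon prescription can be read, this conversion corrects twice and the difference stays at 8.

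**5. Were the arms matched on physical dose instead?** Physical dose = Gy E / RBE.

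- Proton: 10/1.1 = 9.09 Gy.
- Carbon: 18/2 = 9.0, 18/3 = 6.0, 18/4 = 4.5 and 18/5 = 3.6 Gy.
- RBE at which the two are equal: 18/9.09 = 1.98.

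That value is just below the 2 to 5 in the Abstract and outside the 3 to 5 in the effect-size rationale. The article nowhere says that physical dose was matched, and 6 against 5 fractions would differ in any case.

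**The case against.** The strongest reply has four parts.

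**The confirmatory claim is about regimens.** Study design opens by stating the purpose as a carbon boost against a proton boost. Confirmatory Analysis tests equal survival curves and claims superiority of the experimental over the standard treatment. Randomisation identifies that contrast. *This stands.* A reader might infer that the trial or its test is invalid; the documents do not support that.

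**The Background sentence explains the choice of protons over photons.** Both particles share the Bragg peak, and technique is indeed matched: both arms use rasterscanning, prescription to the dose maximum and the 90% isodose as coverage aim. *This stands as context.* The requirement for identical technique need not extend to prescribed dose, and Study design does not repeat it. But the sentence still names RBE as the only contrast, and Study design still credits improvement to carbon biology.

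**The Gy E surplus may be the route through which RBE acts.** At an RBE of 2 to 5, carbon delivers 3.6 to 9.0 Gy physical dose against 9.09 Gy for protons, in smaller physical fractions (3/5 to 3/2 = 0.6 to 1.5 Gy against 2/1.1 = 1.82 Gy). On that reading the surplus exists because RBE is higher. *This stands in part.* It rules out saying that nothing in a result could be due to RBE. It does not restore the aim: the article never gives this reasoning, physical doses agree only near RBE 1.98, and at 3 to 5 the arms are equal neither in physical dose nor in Gy E.

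**The RBE in the effect-size rationale enters no calculation.** *This stands.* A reader might infer that RBE was counted twice in the sample size. The assumed 60% control survival and 20% gain contain no RBE multiplier; the passage is a qualitative justification.

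**Conclusion.** The aim as written cannot be delivered by the design. The comparison mixes a change of particle with 8 Gy E more RBE-weighted boost (18 against 10), 3 against 2 Gy E per fraction, and 6 against 5 fractions. A survival difference cannot be attributed to RBE alone, and the trial cannot show whether carbon has an advantage over protons at equal Gy E.

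This rests only on the stated prescriptions and on the article's own description of Gy E. It needs no assumption about alpha/beta, events or power.

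A reader might go further and say that the carbon boost has about twice the effect of the proton boost. That rests on an assumed alpha/beta and on a conversion that the unit may already contain, so it is an illustration and not a finding.

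The fault is in the stated aim and its interpretation. Endpoint, test, error rate and analysis sets are untouched.

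**What to change.** Reconcile the aim in Background and Study design with the arms in Trial Design and the two Dose Prescription sections. If the regimens stay as written:

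- In Background, delete *solely* and state the aim as a comparison of two boost regimens as prescribed.
- In Study design, replace the attribution to carbon biology with the same wording, and state the permitted conclusion in those terms.
- Say explicitly that the effects of particle, dose and fractionation cannot be separated.
- In item 3 of the sample size section, rest the qualitative rationale for the 20% effect on the difference between the regimens and not on RBE alone.

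No dose or schedule is proposed here. These are wording changes: treatment, sample size and analysis stay as they are. The cost is a more modest mechanistic claim.

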## Methods and Design

### Study design

The purpose of the trial is to compare a carbon ion boost to a proton boost delivered to the macroscopic tumor in combination with combined radiochemotherapy with TMZ in patients with primary GBM.

The aim of the study is to compare overall survival as a primary endpoint, and progression free survival, toxicity and safety as secondary endpoints.

Focus of the analysis is to evaluate the change in overall survival and local control by carbon ion radiotherapy. Therefore, the aim of the trial is to evaluate the improvement in outcome due to effect of the altered biology of carbon ions on GBM. Chemotherapy with TMZ is considered standard treatment and is administered continuously as it would be applied in standard patient care outside any trial.

### Trial Design

The trial will be performed as a single-center two-armed randomized Phase II study. The trial workflow and treatment arms are depicted in Fig. 1.

**Figure 1 F1:**
[figure not shown]
**Workflow diagram of the Cleopatra Study evaluation the role of carbon ion radiotherapy for the treatment of patients with primary glioblastoma**.

Patients fulfilling the inclusion criteria will be randomized into two arms:

Arm A - Experimental Arm

Carbon Ion Radiation Therapy as a Boost to the macroscopic tumor

Total Dose 18 Gy E, 6 fractions, 3 Gy E single dose

Arm B - Standard Arm

Proton Radiation Therapy as a Boost to the macroscopic tumor

Total Dose 10 Gy E, 5 fractions, 2 Gy E single dose

Standard chemotherapy with TMZ will be continued during the experimental and standard arm in conventional dosing of 75 mg/m^2 ^per day.

### Study objectives

The primary objective is overall survival during the follow-up phase of at least 12 months (starting with initial diagnosis).

The secondary objectives of the study are progression-free survival, toxicity and safety.

### Patient selection: Inclusion criteria

Patients meeting all of the following criteria will be considered for admission to the trial:

- histologically confirmed unifocal, supratentorial primary glioblastoma

- macroscopic tumor after biopsy or subtotal resection

- indication for combined radiochemotherapy with temozolomide

- prior photon irradiation of 48-52 Gy to the T2-hyperintense area, resection cavity, areas of contrast enhancement adding 2-3 cm safety margin in combination with standard temozolomide

- registration prior to photon RT or within photon RT allowing the beginning of particle therapy ≤4 days after completion of photon irradiation

- beginning of study treatment (proton or carbon ion RT) no later than 12 weeks after primary diagnosis

- age ≥18 years

- Karnofsky Performance Score ≥60

- adequate contraception.

- Ability of subject to understand character and individual consequences of the clinical trial

- Written informed consent (must be available before enrolment in the trial)

### Patient selection: Exclusion criteria

Patients presenting with any of the following criteria will not be included in the trial:

- refusal of the patients to take part in the study

- previous radiotherapy of the brain or chemotherapy with DTIC or TMZ other than during the radiochemotherapy stated in the inclusion criteria

- more than 52 Gy applied via photon-RT prior to particle therapy

- time interval of >12 weeks after primary diagnosis (neurosurgical intervention) and beginning of study treatment (proton or carbon ion RT)

- Patients who have not yet recovered from acute toxicities of prior therapies

- Clinically active kidney, liver or cardiac disease

- Known carcinoma <5 years ago (excluding Carcinoma in situ of the cervix, basal cell carcinoma, squamous cell carcinoma of the skin) requiring immediate treatment interfering with study therapy

- Pregnant or lactating women

- Participation in another clinical study or observation period of competing trials, respectively.

### Treatment Assignment

Radiation therapy according to the protocol will be performed in patients included into the study and after assignment of the patients to the treatment arms after randomization. Patients withdrawn from the trial retain their identification codes (e.g. randomization number, if already given). New patients must always be allotted a new identification code.

